## Inclusion Criteria for adolescents

- Seeking primary care at the center;
- ages 10-19 years;
- ability to give informed consent;
- availability for duration of interview
- intact cognitive functioning

## Exclusion Criteria for adolescents:

adolescents over 19 years of age, and unable to give informed consent  
 caregiver refusing consent

## inclusion criteria for caregivers

- agree to sign informed consent
- over 18 years of age
- intact cognitive functioning
- availability for duration of interview

#### Sample size

The desired sample size is determined with the goal of obtaining a sample sufficient to estimate the Receiver Operating Characteristic (ROC) curve and Area Under the Curve (AUC) for the tool to be translated, adapted, and validated. While a priori sample size determinations for AUC are highly susceptible to assumptions about the performance of the test (72), a sample size of 100 is generally sufficient to make a qualitative assessment of the utility of a test (73). Given the complexity and multiple assumptions involved, it is customary in validation studies to estimate sample size using comparison with previous validation studies with similar designs.

#### Data collection procedure

##### *Pre-testing phase*

The goals of this phase are to ensure appropriate adaptation of mental health measures for population-level measurement. This will be achieved through translation/adaptation and back-translation, qualitative data collection and analysis using focus groups and interviews.

Additional objectives of the research activities conducted in the initial phase are to gain an in-depth understanding of knowledge and beliefs surrounding adolescent mental health, including causal attributions, risks to mental and emotional well-being in everyday life, and help seeking. Culturally grounded elements of mental health, care and support, and of stigma will be explored. The qualitative data contributes independently to our understanding of culturally salient concepts of mental ill-health, and will improve the quality of the survey measures and ability of mental health interventions to best cater to the needs of adolescents.

##### *Translation/Adaptation (STEP 1)*

A team of 3 individuals with linguistic expertise will review the previously-validated English language tools. They will work together to ensure that the wording is adjusted to be easily and appropriately interpreted in the Kenyan context. Or, they may independently assess the instruments, and meet to discuss areas of discrepancy, ambiguous interpretation, or unclear phrasing. The overall process of translation and adaptation of scales will be guided by the ITC test translation and adaptation guidelines. A Translation Monitoring Form will be used to document the adaptation process and to track incorporation of recommended changes.

##### *Expert Review of Translations (STEP 2)*

The draft version will be presented for review to mental health experts. A second draft version will be created based on feedback from the expert panel. The mental health experts in the technical advisory board would assist us.

##### *Focus Group Discussions (STEP 3)*

Focus group discussions will be conducted with 4 target groups: boys ages 10-14, boys 15-19, girls 10-14, girls 15-19. It is anticipated to have roughly 6-8 adolescents in each group. This process will help in

refining the tools by getting feedback from adolescents in a direct manner as well as on the applicability and sensitivity of the content. A “free listing” exercise may be conducted at the beginning of the focus groups to elicit commonly used words and expressions in the target groups, for example, terms like “sadness” and “worry”. Areas of discrepancy, ambiguous interpretation, or unclear phrasing of questions in the tool will be discussed during the focus groups. The feedback received will be incorporated into the tool and documented in the Translation Monitoring Form.

The discussions aim to first, more generally discuss beliefs about mental illness and its treatment, notions of stigma, sources of support, etc., while the second section of topics will cover aspects of the specific measures and questionnaire items.

Mental health has many components, and is also culturally specific, hence we plan to carefully design the discussion guides, interviews, open-ended questions, and vignettes to uncover aspects specific to the setting. The discussions will tap into ‘what other people think’ about mental illness, care and treatments, and understanding in general surrounding mental illness and well-being. Mental health care utilization and mental health support will be approached with items about mental health services, and non-allopathic modalities, or with inquiring about help seeking behavior in the (fictitious) event of depression or other mental disorder by a member of the household or by using a vignette to this effect. The team of investigators will work collaboratively with local and international experts to develop the discussion guides. Interviews and focus groups may be digitally recorded and transcribed verbatim, and may then be entered into a qualitative analysis software for coding.

#### *Independent Back-translation (STEP 4)*

Back translation of the tool for the original language/setting will then be conducted by someone blind to the original version, to ensure that the original meaning of items is maintained.

#### *Cognitive Interviews (STEP 5)*

Cognitive interviewing will be conducted with a total of 8 adolescents: 2 boys ages 10-14, 2 boys 15-19, 2 girls 10-14, 2 girls 15-19. These interviews will be conducted to garner their understanding of the questionnaire items and to validate the response options. The cognitive interviews will follow a semi-structured interview format. Techniques, such as ‘thinking aloud’ and verbal probing, will be used to ensure that items are correctly understood, and to identify problems with wording and/or difficulties with response options. The specific items in the questionnaire will be discussed, to confirm the validity of the item adaptation, assess suitability and interpretation of the response options, and to understand the process whereby their response was chosen. Areas of discrepancy, ambiguity, or unclear phrasing of items or response choices will be discussed during the interviews. The data gathered will be used to guide further adaptation or modifications to ensure reliability of data in the next phase of testing, and will be documented in the Translation Monitoring Form.

In order to reduce participant burden, participants may be encouraged to focus on items which they identified as being particularly difficult or easy to understand, or those which they feel could be rephrased to improve clarity. Each cognitive interview is anticipated to last 30 minutes up to 1 hour. Based on feedback obtained during cognitive interviews, a revised version of the questionnaire will be finalized.

The research team will work collaboratively to develop the interviewing guides, and as well to provide training to the research staff.

## I. Questionnaire administration and validation phase

### *Questionnaire Administration (STEP 6)*

Survey questionnaires will be administered to 250 adolescents and 100 parents of younger adolescents. Surveys may be administered within the school context or at home, depending on school-year and feasibility assessment of the setting. The questionnaire will be administered by research assistants using manually the entire tool, including all optional test modules, is anticipated to take 30 minutes or less to administer. As part of this work all research assistants will receive basic tool administration training and be fluent in English.

A preliminary draft of the measures (instruments) planned for inclusion in the survey is provided in the Appendix 44-55. The final revisions of tools will be informed by the qualitative data results. Cards with written response options may be made be available to all respondents. Specific images and response items on the cards will have been previously validated during the focus groups and cognitive interviews. A selection of 50 participants will be asked to complete the questionnaire a second time, 1-2 weeks following the initial administration – to allow for test-retest analysis of the stability of the measures.

### *Validation Procedures (STEP 7)*

Validation using diagnostic interview by trained mental health worker/ psychosocial counselor A sub-sample of 50 individuals scoring above the cut-off for each condition (anxiety, depression, suicidal ideation or attempt, and behavioral or conduct problems), and 50 or more healthy individuals (controls) will be re-contacted to be administered a diagnostic interview, such as the Kiddie-SADS. The K-SADS is prioritized as it can be administered by a child and adolescent mental health professional with any level of training, ideally mental health nurses, counselors, or social workers. Approximately 30 minutes to 1 hour is the estimated duration for each administration of the diagnostic interview, as only the portions relevant to this study will be administered (introductory interview portion, depressive disorders, anxiety disorders, attention deficit hyperactivity disorder, oppositional defiant disorder, conduct disorder. The diagnostic interview will take place in a room or office arranged for the study purposes, or location convenient to the participant, such as at a nearby clinic, a school or their home. The privacy and safety of the participant will be prioritized. Clinical calibration using K-SADS would be carried out by a team of county and MOH psychiatrists who are part of the study implementation work.

Primary outcome measures of the survey and validation phase include depression, anxiety, behavioral problems, suicidal ideation or attempt, and functional impairment due to any mental health condition. Secondary outcome measures may include health risk or protective behaviors, like substance use, physical activity, experience of violence or abuse, or bullying. Household variables may include socio-economic characteristics and composition of the household and household members, and other established risk or protective factors at the individual, family, or community level, that are relevant to adolescent mental health. **Participants with high scores will receive 4 sessions brief IPT to help manage some of their issues.**

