## 2.2 Aims and Objectives

### Aim 1 (1-18 months).

To explore multi-level implementation barriers, and facilitators to implementation of mhGAP-perinatal depression care guidelines in pregnant adolescents in Kenya. A secondary aim would be to explore the mental health treatment preferences of pregnant adolescents.

- 1.1 To identify multilevel implementation barriers to the implementation of perinatal depression care in pregnant adolescents
- 1.2 To identify multilevel implementation facilitators to the implementation of perinatal depression care in pregnant adolescents.
- 1.3 To understand treatment preferences of pregnant adolescents using conjoint analysis informed by barriers and facilitators (1.1 and 1.2)
- 1.4 To carry out a psychometric evaluation of brief depression, anxiety, suicidality and general functioning tools with general sample of adolescents and pregnant adolescents to develop more sustainable assessments in primary care

**Aim 2 (19-30 month).** To use Aim 1 findings to develop adapted version of IPT-G/and mhGAP-IG and build MCH capacity for implementation.

- 2.1 To adapt the mhGAP to Kenyan adolescents and maternal child health contexts.
- 2.2 To adapt the G-IPT to Kenyan adolescents and maternal child health contexts.
- 2.3 To employ a user-centered design to adapt the face-to-face training of mhGAP/IPT-G to an e-version and study the feasibility, acceptability, and usefulness of the e-version of the mhGAP/IPT-G training for health care workers (both health facility staff and community health workers).
- 2.4 To collaborate with MOH and primary care and community service stakeholders that we have built collaboration relationship with as part of the K to plan and pilot test the e-version of mhGAP/IPT-G training in 2-3 service settings (e.g., KNH, Mathari, and Ngara primary health care centre). The research implementation team will provide technical support to service stakeholders/leaders on e-version of mhGAP/IPT-G training and implementation, and to estimate the impacts of the e-training on their clinical service and patient's mental health outcomes.
- 2.5 To build maternal child health capacity to implement the adapted programs by training

HCWs in online training integrating mhGAP/IPT-G through the Fogarty K43 COVID supplement

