We intend to add a short exercise of pilot testing of a set of brief tools that have been recommended for MICS data collection on mental health indicators for adolescents in LMICs. These tools are briefer, simpler and currently being tested with adolescents in Belize and South Africa. These tools cover depression, anxiety, suicidality and functional impairment using Revised Children's Anxiety and Depression Scale (RCADS) (71)

We will test these tools on ages 10-14 and 15-19 years in our study sites. The tools which were listed as part of the intervention have been developed for adults though tested on adolescents.

The overall aim of this exercise is to establish the validity and reliability of measures of adolescent mental health, using multiple qualitative and quantitative approaches, including focus groups, translation/back translation, clinical evaluation, and psychometric analyses.

The specific objectives are

1a) Examine the content validity of tool items within each of the tools for the Kenyan context, using focus group discussions and interviews, and appropriateness of items using cognitive interviewing techniques.

1b) Validate the key measures of mental health for adolescents for a questionnaire module against a gold standard diagnostic interview and classical and modern psychometric analyses.

2: Explore mental illness stigma, help seeking behavior, perspectives on access to social support, mental health care or social services utilization, and knowledge about mental health, using focus groups.

3: Understand younger and older adolescents' conceptions of mental health and wellbeing and how proposed intervention materials can be adapted to best suit Kenyan adolescents, and how materials could be adapted for pregnant and parenting adolescent populations in various LMIC settings.

Table 1b: questionnaire testing phases, steps and relevant activities

| Phase                         | Step | Activity                                                                                                                                                                                                |
|-------------------------------|------|---------------------------------------------------------------------------------------------------------------------------------------------------------------------------------------------------------|

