#### *Statistical Analysis*

Quantitative data will be analyzed using a statistical software package. Analyses will be conducted to assess the performance of the tool using clinical diagnoses according to K-SADS as the gold standard. Analyses will also be conducted to assess the performance of individual questionnaire items. Diagnostic sensitivity and specificity, positive predictive value, negative predictive value, positive likelihood ratio, negative likelihood ratio, diagnostic odds ratio, Youden's index and reliability will be calculated. Curve analysis will be used to determine the optimal cut-off. Internal consistency of the subscales will be assessed. Cronbach's  $\alpha$  values will be calculated for the total scale and subscales identified by factor analysis. As factor analysis is planned, to confirm meaningfulness of item clusters, sufficient sample size for this has been estimated. Values of 0.80, or higher, are commonly accepted as evidence of adequate internal reliability. An 'if item deleted' analysis will be conducted to identify whether any items should be dropped from the scale.

To assess test-retest reliability, intraclass correlation coefficients will be calculated on subscale and total scores which are expected to remain stable. Weighted Cohen's  $\kappa$  values may be also calculated to assess test-retest reliability at the item level. Coefficients will be established separately for children and adults, and on samples of approximately 50 questionnaires completed approximately 1-2 weeks after initial completion.

Intraclass correlations will be used to assess inter-rater agreement between pairs of scores from different raters (e.g., self-report vs. parent). Coefficients will be calculated at the subscale and total score levels. Weighted Cohen's  $\kappa$  values will also be calculated to assess inter-rater reliability at the item level.

Receiver operating characteristic (ROC) analyses will be conducted to evaluate the discriminative ability of the tools. Analyses will be conducted comparing to the presence of clinical diagnosis according to the Kiddie-SADS. In addition, independent samples t tests will be performed with clinical diagnoses to assess if there are differences in tool scores and assess the ability of the tools to distinguish between diagnoses.

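### Suicidality is a primary measure and a cut-off condition in the Aim 1 tool validation, but the protocol names no reference criterion for it in the diagnostic interview

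*Protocol*

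**What the plan says.** The validation work sits under Aim 1. Objective 1.4 in section 2.2 is "To carry out a psychometric evaluation of brief depression, anxiety, suicidality and general functioning tools" in general and pregnant adolescents. Objective 1b in section 3.3 adds that the key measures are to be validated against a gold standard diagnostic interview, together with psychometric analyses.

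Validation Procedures (Step 7) then fixes three things:

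- The outcomes: "Primary outcome measures of the survey and validation phase include depression, anxiety, behavioral problems, suicidal ideation or attempt, and functional impairment".
- Who is interviewed: "A sub-sample of 50 individuals scoring above the cut-off for each condition (anxiety, depression, suicidal ideation or attempt, and behavioral or conduct problems", plus 50 or more controls.
- What the interview contains: it is kept short, "as only the portions relevant to this study will be administered (introductory interview portion, depressive disorders, anxiety disorders, attention deficit hyperactivity disorder", and the list ends with oppositional defiant disorder and conduct disorder.

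The Statistical Analysis text sets the reference: "Analyses will be conducted to assess the performance of the tool using clinical diagnoses according to K-SADS as the gold standard". Diagnostic accuracy indices, ROC analysis and the choice of optimal cut-off follow, and no measure is exempted. The ROC comparison is with whether a K-SADS diagnosis is present.

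**The concern.** A diagnostic accuracy study needs a reference result for the construct that the index test claims to measure. For suicidality the protocol has an index score, a cut-off and a plan to interview high scorers, but the interview as described names nothing that yields a suicidality result.

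If the analysis text is followed, the only reference available is a depressive, anxiety or behavioural diagnosis. The resulting sensitivity or cut-off would describe how well a suicidality item detects another disorder, yet it could be reported as validity for suicidality. The protocol presents the work as locally validated measurement for pregnant and parenting adolescents, with possible later use in national data collection, so the label matters.

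This cannot safely be left to a later analysis plan. A reference standard is collected at the interview, and one that was never recorded cannot be recovered afterwards.

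**Working it through.** No sample size, power or error-rate figure is involved, so the check sets the texts side by side. Inputs are the primary measures, cut-off conditions and interview portions from Step 7, and the reference rule from Statistical Analysis.

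| Primary measure | Cut-off leads to interview | Matching interview portion named | Other criterion stated |
|---|---|---|---|
| Depression | yes | depressive disorders | none needed |
| Anxiety | yes | anxiety disorders | none needed |
| Behavioural problems | yes | ADHD, oppositional defiant, conduct | none needed |
| Suicidal ideation or attempt | yes | none | none |
| Functional impairment | no | none | none |

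**Reference side.** Three of the five measures have a matching interview portion, so 5 − 3 = 2 do not. Among the four conditions with a cut-off, 4 − 3 = 1 has no matching portion: suicidality.

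**Suicidality under the stated rule.** The rule compares the score with a K-SADS diagnosis. The portions listed lead to depressive, anxiety, attention-deficit, oppositional defiant or conduct diagnoses. None of these is suicidal ideation or attempt. The analyst is left with no accuracy estimate, or with one against another construct.

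**Functional impairment under the stated rule.** It has no reference diagnosis, and it is absent from the list of cut-off conditions, so no cut-off for it is visibly planned. Content validity, internal consistency, factor structure, test-retest reliability and agreement between self-report and parent report can all be obtained. The planned t tests of tool scores by diagnosis also give a known-groups comparison. That is sensible here, because Step 7 describes impairment as arising from any mental health condition.

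**Index side.** Section 3.3 says of the brief tools: "These tools cover depression, anxiety, suicidality and functional impairment using Revised Children's Anxiety and Depression Scale (RCADS". Tools are therefore stated for suicidality and functioning, and the gap for both lies only in the reference. The same sentence and objective 1.4 leave out behavioural problems, which Step 7 includes as an outcome, a cut-off condition and three interview portions. These texts do not agree. Step 6 places the draft instruments in Appendices 44 to 55, which include the two-part MMAP adolescent questionnaire (50 and 51), and that content is not shown.

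**The case against.** The strongest reply has three parts.

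First, no single sentence promises K-SADS accuracy for all five measures. The five are outcomes of the survey and validation phase together, and objective 1b pairs the interview with psychometric analyses. This stands. A reader might infer that the protocol promises accuracy for functional impairment and cannot deliver any validity for it. The text does not support that: no cut-off is stated and several forms of evidence remain.

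Second, one of the listed portions may already record suicidal ideation or attempts, and the K-SADS is itself given in Step 7 only as an example of a suitable interview. The protocol cannot settle what the portions contain. Even if an item is there, the Statistical Analysis text makes presence of a clinical diagnosis the comparator, not an item rating. The objection shows that the remedy is easy, but it does not supply the missing reference.

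Third, this is formative tool testing, separate from the randomised comparison in Aim 3, and matching subscales to reference variables is often left to an analysis plan. The first half is right and limits the weight of the point. The second half would hold if the data were certain to be collected, which the list of portions does not ensure.

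A reader might also conclude that only depression and anxiety have both a tool and a reference, that no behavioural tool exists, and that the behavioural stratum and its modules should go. The documents do not support this. The relevant appendices are not shown, and a stated cut-off for behavioural problems implies a scored measure.

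**Conclusion.** The point holds for suicidality. It is a primary measure and one of the four conditions that select participants for interview, it is subject to an accuracy analysis defined by K-SADS diagnoses, and it has no stated reference criterion. Criterion accuracy and any cut-off for it are undefined, or belong to another construct.

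For functional impairment the point is smaller: no reference criterion is stated, so no diagnostic accuracy should be claimed, but its reliability and its content and known-groups validity are not in doubt on this ground. The omission of behavioural problems from the description of the tools is an inconsistency to reconcile, not evidence of a missing tool.

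This rests on reading objective 1b, Step 7 and Statistical Analysis together, and on taking the list of interview portions as complete, as its wording indicates. It should be corrected before the validation interviews begin. It does not affect the Aim 3 trial analysis.

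**What to change.** In Validation Procedures (Step 7), state that the interviewer records suicidal ideation or attempt as a separate reference variable during the same interview. This works whether or not a listed portion already asks about it.

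In Statistical Analysis, compare the suicidality measure with that variable and not with a depressive or other diagnosis. Limit sensitivity, specificity, ROC and cut-off claims to measures with a matching reference. For functional impairment, claim only reliability and convergent or known-groups validity.

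Reconcile the description of what the brief tools cover, and objective 1.4, with the inclusion of behavioural problems in Step 7, by naming the behavioural measure or pointing to the appendix that holds it. The behavioural stratum and interview portions stay.

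The cost is one added interview field and a few sentences. The downside is that no K-SADS cut-off is claimed for functioning.
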